### 2.3 Randomization 

Randomization will be performed by a statistician who does not take part in the 
study. All eligible participants will be allocated into four groups using a 
computer-generated random number table. Each assigned a specific group number: 
HD-tDCS + CCRT (Group 1), HD-tDCS (Group 2), CCRT (Group 3), and control (Group 
4). For the randomization process, personnel employed Microsoft Excel 2019 
software (Microsoft Corp., Redmond, WA, USA) to enter 48 participants into a spreadsheet, assigning each a unique 
identifier ranging from “1–48”. They then used the “=RAND()” function to 
generate a random number for each assigned number. Subsequently, these random 
values were fixed using the “Paste Special” dialog box. Following this, the fixed 
random values were sorted in descending order. The sorted numbers were then 
divided into four groups, each comprising 12 numbers, resulting in a total of 48 
numbers. This procedure effectively randomized the 48 patients into four groups, 
with each group consisting of 12 individuals. Once the randomization scheme was 
established, it was secured in opaque envelopes, which were opened sequentially 
according to the order of participant enrollment. The allocation scheme within 
each envelope determined the group assignment for each patient. This method 
ensured that study personnel could not compromise the randomization process by 
having prior knowledge of the randomization scheme. The progression of 
participants through the screening, randomization, therapy, and follow-up stages 
is illustrated in Fig. 2.

**Fig. 2. S3.F2:**
[figure not shown]
**The flow diagram of the research design**.

### 2.4 Blinding

Throughout the study period, both participants and evaluating psychiatrists 
remained blinded. In implementing blinding procedures, we will adhere to these 
considerations and measures. The specific group assignments of patients will be 
disclosed only to the principal investigator. Patients were unaware of the 
details of allocation sequences and were explicitly instructed not to discuss 
with each other any aspects of group allocation, received therapies, 
questionnaire completion, or other experimental procedures. Participants will 
keep unaware of the allocation sequences and will be explicitly instructed not to 
discuss any aspects of group allocation, receive therapies, questionnaire 
completion, or other experimental procedures. To minimize potential interference 
with blinding by therapy personnel, we will employ four distinct therapy groups, 
each responsible for implementing their respective therapies. Each group was 
informed only of their own protocol and had no knowledge of group allocation 
details or the therapy plans of other groups. Communication between groups 
regarding specific therapy content will be strictly prohibited. During the 
experimental phase, the principal investigator will provide each group with the 
specific protocol for their corresponding group, after which each group will 
implement the therapies for their assigned patients. During the outcome 
measurement phase, personnel responsible for data collection and analysis will 
keep blinded to group allocation and specific therapy. The principal investigator 
implemented a “two-stage unblinding” procedure. Once the data was locked, the 
initial unblinding was conducted, dividing the data into Groups 1–4 without 
disclosing their actual relationships or true assignments. The unblinding will be 
conducted after the data analysis is completed, clearly indicating the specific 
group representations of 1–4.

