## 2. Methods

### 2.1 Study Design 

This study is a prospective, double-blind, randomized controlled trial protocol 
to assess the efficacy of HD-tDCS combined with CCRT in enhancing cognitive 
function among patients with schizophrenia. Eligible participants will be 
recruited and randomly allocated into four groups using a random number table: 
the HD-tDCS + CCRT group (Group 1), the HD-tDCS group (Group 2), the CCRT group 
(Group 3), and the control group (Group 4). Assessments will be carried out at 
baseline (T0), after 10 sessions (T1), after 20 sessions (T2), and after six 
months of follow-up (T3). Research framework is illustrated in Fig. 1. 
Participants in the control group (Group 4) will continue to receive their stable 
regimen of antipsychotic medication and standard clinical care, without 
undergoing any HD-tDCS or CCRT sessions.

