	(2) Organic brain lesions, intellectual disabilities, or other severe physical illnesses.
	(3) Currently undergoing other neurostimulation therapies or evidence - based psychotherapy.
	(4) There are indications related to contraindications for HD-tDCS.
	(5) There are visual impairments or significant eye diseases, such as color blindness, color weakness, cataracts, etc.
	(6) Substance abuse and addiction.
	(7) Women who are pregnant or breastfeeding.
Study Type	Interventional
	Allocation: randomized
	Masked: double blind
	Primary purpose: schizophrenia intervention
Date of First Enrollment	June 2025
Sample Size	48
Recruitment Status	Pending
Primary Outcome(s)	(1) MATRICS Consensus Cognitive Battery (MCCB)
	(2) Brief Psychiatric Rating Scale (BPRS)
	(3) Positive and Negative Syndrome Scale (PANSS)
Key Secondary Outcomes	(1) Clinical Global Impressions (CGI)
	(2) Social Disability Screening Schedule (SDSS)
	(3) Schizophrenia Quality of Life Scale (SQLS)
	(4) Magnetic Resonance Imaging (MRI)
	(5) General Information Questionnaire (GIQ)
	(6) Adverse Reaction Scale (ARS)
	(7) Serum levels of Brain-Derived Neurotrophic Factor (BDNF)
	(8) Serum levels of Glial Cell Line-Derived Neurotrophic Factor (GDNF)
Ethics Review	Approved (Approval Number: XYEFYLL-2025-15)
	Approval Date: 17 February 2025
	The Second Affiliated Hospital of Xinxiang Medical University. [contact], [name]
Completion date	Pending
Summary Results	Pending
IPD sharing statement	N/A

The research could be halted under the following conditions: (1) the occurrence 
of an unexpected medical emergency; (2) the emergence of severe side effects or 
adverse events that preclude the continuation of the study; or (3) the withdrawal 
of informed consent by the participant or their family. It is imperative that 
participants have maintained a stable dose of antipsychotic medication at least 
two weeks, and that this dosage remains unchanged throughout the study duration. 
During the therapy, participants will continue to receive their routine daily 
treatment.

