### 2.6 MRI-guided High-Definition Transcranial Direct Current 
Stimulation

MRI scans will be employed to construct detailed anatomically realistic head 
models. The development and simulation of head models for the HD-tDCS-induced 
electric field use the SimNIBS software (version 4.5, SimNIBS Group, Copenhagen, 
Denmark) [30]. Eight distinct 4*1 montages centered on the mPFC will be used to 
simulate the E-field for each brain. The normal component of the E-field will be 
calculated using the finite element method [31]. Based on T1 and T2 MRI scans, 
head models will be constructed from these images, incorporating five different 
tissues: skin, skull, white matter, gray matter, and CSF. Finally, the mPFC will 
be identified in each subject’s brain according to the Ranta atlas [32]. The 
study will utilize an MRI-guided HD-tDCS device (model MxN-9-9002A, Soterix 
Medical, New York, NY, USA). The central electrode will be positioned over the 
mPFC. The four surrounding cathodes will be positioned at frontal sites Fp1, Fp2, 
F7, and F8. The current intensity will be maintained at 2 mA. Each HD-tDCS 
session will involve the delivery of a 2 mA direct current for a duration of 30 
minutes. HD-tDCS will be conducted 5 times per week, over a 4-week period, 20 
sessions. During the therapy period, patients will continue their existing 
pharmacological treatment regimens without any modifications.

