### 2.9 Outcome

The primary outcome measure used in this research is the MATRICS Consensus 
Cognitive Battery (MCCB), which is a crucial tool for assessing cognitive 
deficits in schizophrenia. It evaluates seven distinct cognitive domains: working 
memory, abstract thinking, attention/vigilance, processing speed, visual 
learning, verbal/visual learning, reasoning and problem-solving. The battery 
comprises the following subtests: (1) Trail Making Test A (TMT-A), (2) Symbol 
Coding, (3) Hopkins Verbal Learning Test-Revised (HVLT-R), (4) Digit Span Test 
(DST), (5) Stroop Color-Word Test, (6) Spatial Span Test (derived from the 
Wechsler Memory Scale III, WMS-III), (7) Verbal Fluency Test (VFT), (8) Mazes, 
(9) Brief Visuospatial Memory Test-Revised (BVMT-R), and (10) Continuous 
Performance Test-Identical Pairs (CPT-IP).

Secondary outcome measures include the Brief Psychiatric Rating Scale (BPRS), 
the PANSS, the Clinical Global Impression 
(CGI) scale, the Social Disability Screening Schedule (SDSS), the Schizophrenia 
Quality of Life Scale (SQLS), and fMRI. Specifically, the general information 
questionnaire is utilized to collect basic information about the patients. BPRS 
primarily assesses the severity of psychotic symptoms, with total scores ranging 
from 18 to 126, where higher scores reflect more severe symptoms. PANSS is used 
to evaluate the presence and severity of various symptoms. CGI scale is applied 
to assess the patient’s overall condition and therapeutic efficacy. SDSS measures 
the extent of social functional deficits. SQLS is designed to evaluate the 
quality of life in schizophrenia. For detailed information, please see Table 2.

**Table 2. S3.T2:** **Schedule of enrollment, interventions, assessments, and visits 
of patients**.

	Recruitment	Baseline	Assessments		
			Weekend 2	Weekend 4	6-month follow-up
Time point		T0	T1	T2	T3
Prescreening for eligibility, consenting and clinical interview					
Recruitment					
Eligibility screening	√				
Informed consent	√				
Allocation	√				
Primary outcome assessment					
MCCB		√	√	√	√
Second outcome assessment					
BPRS		√	√	√	√
PANSS		√	√	√	√
CGI		√	√	√	√
SDSS		√	√	√	√
SQLS		√	√	√	√
GIQ		√			
MRI		√	√	√	√
Blood sample collection (BDNF and GDNF levels)		√		√	√
Safety					
ARS			√	√	

A checkmark (√) indicates the time point at which each assessment is 
carried out. MRI, magnetic resonance imaging.

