thinning [74]. Individuals with chronic, untreated schizophrenia exhibit more 
pronounced progressive deterioration of brain structures—such as reductions in 
gray matter volume, diminished white matter integrity, and disrupted brain 
network connectivity—compared to those who have been recently diagnosed or 
treated [75]. These findings suggest that the complex interplay between the 
pathophysiological processes of the disease and its pharmacological management 
may influence the therapeutic efficacy of both HD-tDCS and CCRT. Future research 
should incorporate subgroup analyses based on illness duration to specifically 
investigate how these factors may moderate the interaction between HD-tDCS and 
CCRT.

This study still has some limitations. Firstly, the relatively small sample size 
might influence the statistical power and limit the generalizability of the 
outcomes. Future research should consider increasing the sample size to enhance 
statistical robustness. Secondly, the absence of a double-sham control group, 
which would receive both sham HD-tDCS and a sham version of CCRT, complicates the 
ability to definitively differentiate between specific therapeutic effects and 
potential placebo effects. Additionally, the lack of corresponding sham controls 
for the HD-tDCS-alone and CCRT-alone groups constrains our capacity to accurately 
assess the independent contributions of each monotherapy. Thirdly, we intend to 
collect resting-state fMRI data, which could not provide task-specific 
information. Future study will employ task state fMRI to reflect the fMRI images 
of the brain when performing specific tasks. Finally, the mechanisms underlying 
the combined therapy remain relatively unexplored, particularly regarding how 
these two modalities synergistically enhance cognitive function through specific 
pathways. This necessitates further comprehensive research to elucidate these 
mechanisms.

This study protocol establishes an important theoretical framework for exploring 
the combined therapy and provides guidance for future research. Using MRI-guided 
HD-tDCS targeting mPFC will enhance the development of individualized therapies 
for schizophrenia. Findings from multimodal neuroimaging and blood biomarkers 
could uncover the mechanisms of combining MRI-guided HD-tDCS with CCRT for 
schizophrenia and contribute to develop more individualized approaches. As a 
result, this integrated therapeutic strategy holds significant promise for 

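### The protocol claims a double-blind trial with blinded participants, but no arm has a sham; only assessor blinding is supported

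*Protocol article*

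**What the plan says.** Section 2.1 states: "This study is a prospective, double-blind, randomized controlled trial protocol". Table 1 in section 2.2 gives "Masked: double blind", and the Discussion uses the double-blind label twice more. Section 2.4 extends the claim to named roles: "Throughout the study period, both participants and evaluating psychiatrists" are said to remain blinded.

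On what each arm receives, section 2.1 says that Group 4 continues its medication and usual care without "undergoing any HD-tDCS or CCRT sessions". Section 2.6 says that each HD-tDCS "session will involve the delivery of a 2 mA direct current for a duration of 30" minutes, over 20 sessions, and mentions no sham mode. Section 2.7 gives 20 sessions of computer training and no sham training. The limitations in section 4 name the "absence of a double-sham control group" and add that the two single-therapy arms have no sham counterpart either.

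On the data, section 2.4 sets out a two-stage procedure: after lock, the "initial unblinding was conducted, dividing the data into Groups 1–4 without" revealing the real arms, which are identified once the analysis is finished. Sections 2.1 and 2.3 use the numbers 1 to 4 as the names of the arms.

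On timing, Table 2 ("Schedule of enrollment, interventions, assessments, and visits" of patients) ticks Allocation under Recruitment, one column before the T0 assessments.

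**The concern.** A patient knows whether electrodes were placed on the scalp and whether computer tasks were done. The arms differ in exactly these visible ways, so the participant half of the double-blind claim describes a property that the design does not have.

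The primary outcome, the MCCB, is a performance battery on which effort and expectation can matter even when the tester is blind. Non-specific gains from attending a programme can enter the contrasts with the no-session control, and possibly the interaction that is meant to show synergy. A reader who relies on the label, or on the registration table that carries it, would assume a protection against this bias that is absent.

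Two lesser matters concern the same safeguard. The masked dataset carries labels that match the published arm numbers, and the schedule places allocation ahead of baseline testing.

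**Working it through.** **Step 1. Claim against design.** There is no stated figure to reproduce, so the check sets the sections side by side.

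| Arm | HD-tDCS | CCRT | Sham of the missing component |
|---|---|---|---|
| Group 1 | active, 20 sessions | active, 20 sessions | not applicable |
| Group 2 | active, 20 sessions | none | none |
| Group 3 | none | active, 20 sessions | none |
| Group 4 | none | none | none |

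Arms with any sham component: 0 of 4 (sections 2.1, 2.6, 2.7 and 4). The measures in section 2.4 are concealment of the sequence, a ban on discussion between patients, and a separate therapy team for each arm. They limit what a patient learns about others. None hides from a patient, or from the treating team, what that patient is given.

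**Step 2. What is supported.** Section 2.10 gives the scale assessments to physicians outside the trial who are blinded, which agrees with the assessor part of section 2.4. Nothing in the documents contradicts it.

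**Step 3. Possible effect on the contrasts.** Let g1 to g4 be the non-specific gain in each arm, with g4 = 0 because Group 4 attends no sessions. The bias in a contrast is the same contrast applied to the g values. For the interaction it is g1 − g2 − g3 + g4.

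| Pattern of non-specific gain | G2−G4 and G3−G4 | G1−G4 | G1−G2 and G1−G3 | Interaction |
|---|---|---|---|---|
| Equal: g1 = g2 = g3 = p | +p | +p | p − p = 0 | p − p − p + 0 = −p |
| Additive: g1 = 2p, g2 = g3 = p | +p | +2p | 2p − p = +p | 2p − p − p + 0 = 0 |
| More than additive: g1 = 2p + d, d > 0 | +p | 2p + d | p + d | 2p + d − p − p + 0 = +d |

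The documents give no value for p. With p assumed at 0.2 to 0.4 SD, the single-therapy contrasts with Group 4 are overstated by 0.2 to 0.4 SD under all three patterns. The interaction is understated by 0.2 to 0.4 SD under the first, unaffected under the second and overstated by d under the third. Both the size of p and the pattern are assumptions.

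**Step 4. Dataset labels.** The published names are Groups 1, 2, 3 and 4, and the first-stage labels are also Groups 1 to 4. No permutation is stated. In addition, section 2.11 plans to compare training accuracy and reaction time between Groups 1 and 3. Only those two arms can have such data, so an analyst holding the training logs can pick out the two CCRT arms whatever the labels are.

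**Step 5. Timing of allocation.** Table 2 places Allocation under Recruitment. Section 2.3 says that envelopes are opened in order of enrolment, without saying whether this is before or after T0.

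**The case against.** The strongest reply is that the limitations already disclose the missing shams and say that specific and placebo effects cannot be definitively separated. Outcome assessment is also in the hands of blinded outside physicians. Both points are true. The remaining fault is therefore a wrong label on a partly disclosed limitation, not a hidden one. But the limitations paragraph does not withdraw the claims in sections 2.1 and 2.4, Table 1 or the Discussion itself, and disclosure in one place does not correct a contrary statement in four others. One could also read participant blinding as ignorance of the allocation sequence only. That is allocation concealment, and it is not what double-blind conveys.

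Three stronger readings may tempt a reader, and the documents do not support them.

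- **That analysts demonstrably hold the key.** Section 2.4 says that the first-stage labels do not reveal the true arms and that their meaning is given later, which suggests that they may be permuted. Reusing the arm numbers is an ambiguity, not proof. Nor does the factorial model by itself force unmasking. A four-level group factor gives the same fit as the 2 × 2 model, and four masked labels allow only three possible pairings for the interaction, so the right one can be chosen after the key is opened.
- **That patients know their arm at the baseline MCCB.** The Recruitment column is not a dated visit, section 2.4 restricts knowledge of assignments to the principal investigator, and the flow figures are not available here. The tick leaves the possibility open and shows no more.
- **That synergy is necessarily masked.** This holds only if the gain is equal in Groups 1 to 3. Under that same pattern, the hypothesised comparisons of combined against single therapy carry no bias.

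**Conclusion.** The double-blind label and the statement that participants are blinded are wrong as written. With no sham in any of four visibly different arms, participants and therapists know what is given. The trial is assessor-blinded, and that part stands. This conclusion rests on the text alone and needs no numerical assumption.

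The size of the consequence is conditional. Contrasts with Group 4 estimate therapy together with expectation and contact. The interaction may be biased downwards, not at all or upwards, depending on how non-specific gains combine, and the documents cannot settle which. The range of 0.2 to 0.4 SD is an illustration, not an estimate.

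The dataset labels and the Allocation tick are secondary. Each is an ambiguity worth closing; neither shows that blinding of analysts or of the baseline has failed.

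**What to change.** 1. In sections 2.1 and 2.4, Table 1, the registry entry and the Discussion, replace the double-blind label and the participant-blinding statement with: assessor-blinded, open to participants and therapists.
2. State that contrasts with Group 4 estimate therapy plus expectation and contact. State also that the HD-tDCS × CCRT interaction may be biased in either direction, depending on how non-specific gains combine across arms.
3. Label the locked dataset with neutral permuted codes. The key could be held by the outside statistician who performs the randomisation. Keep the CCRT logs apart until the main analysis is done, and lock the analysis script before the key is opened.
4. Open each envelope only after that patient's T0 assessments are complete, and move the Allocation tick in Table 2 to match.

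The cost is a less favourable design label, a registry update, a change in when envelopes are opened, and minor data-handling work: recoding, holding the key, separating the logs and locking the script. Arms, sample size and patient care are unchanged, and no sham arm is being asked for.

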### 2.5 MRI Scanning

All participants will receive MRI scans at T0, T1, T2, and T3. MRI scans will be 
conducted in the Department of Radiology at the Second Affiliated Hospital of 
Xinxiang Medical University. The scanning procedures will be performed by 
radiologists who are proficient in MRI operation. A 3.0T MRI scanner (MAGNETOM 
PRISMA, Siemens Healthineers, Erlangen, Germany) will be used for the scans. 
Structural T1-weighted MRI images will be acquired using a 3D MPRAGE sequence 
with the following parameters: Field of View (FOV) = 224 × 224, flip 
angle = 8 degree, Repetition Time (TR) / Echo Time (TE) / Inversion Time (TI) = 
2400/2.14/1000 ms, voxel size = 0.7 mm isotropic, Bandwidth (BW) = 210 Hz/pixel, 
integrated Parallel Acquisition Techniques (iPAT) = 2. T2-weighted images will be 
obtained using a 3D T2-SPACE sequence, with the following parameters: TR/TE = 
3200/565 ms, flip angle variable, FOV = 224 × 224, voxel size = 0.7 mm 
isotropic, BW = 755 Hz/pixel, iPAT = 2. Resting-state MRI data will be acquired 
using a gradient echo planar imaging sequence with the following parameters: TR = 
2000 ms, TE = 30 ms, FOV= 220 mm × 220 mm, slice thickness = 4 mm, 
inter-slice gap = 0.6 mm, number of slices = 33, in-plane resolution = 64 
× 64, flip angle = 90°.

### 2.6 MRI-guided High-Definition Transcranial Direct Current 
Stimulation

MRI scans will be employed to construct detailed anatomically realistic head 
models. The development and simulation of head models for the HD-tDCS-induced 
electric field use the SimNIBS software (version 4.5, SimNIBS Group, Copenhagen, 
Denmark) [30]. Eight distinct 4*1 montages centered on the mPFC will be used to 
simulate the E-field for each brain. The normal component of the E-field will be 
calculated using the finite element method [31]. Based on T1 and T2 MRI scans, 
head models will be constructed from these images, incorporating five different 
tissues: skin, skull, white matter, gray matter, and CSF. Finally, the mPFC will 
be identified in each subject’s brain according to the Ranta atlas [32]. The 
study will utilize an MRI-guided HD-tDCS device (model MxN-9-9002A, Soterix 
Medical, New York, NY, USA). The central electrode will be positioned over the 
mPFC. The four surrounding cathodes will be positioned at frontal sites Fp1, Fp2, 
F7, and F8. The current intensity will be maintained at 2 mA. Each HD-tDCS 
session will involve the delivery of a 2 mA direct current for a duration of 30 
minutes. HD-tDCS will be conducted 5 times per week, over a 4-week period, 20 
sessions. During the therapy period, patients will continue their existing 
pharmacological treatment regimens without any modifications.

